## Abstract

**Background:**

Pancreatoduodenectomy (PD) is traumatic, difficult to perform, and has a high incidence of postoperative complications and perioperative mortality. Postoperative complications and pain occur frequently and seriously affect the psychological status of patients. Esketamine, an N-methyl-D-aspartate (NMDA) receptor antagonist, has analgesic and antidepressant effects. In this study, we aim to investigate the effect of esketamine on postoperative depression and pain in patients undergoing PD.

**Methods/design:**

This prospective, single-center, randomized control trial will include 80 patients who will undergo elective PD. The patients will be randomly assigned to two groups: the experimental group that will receive esketamine (*n* = 40) and the control group (*n* = 40). In the esketamine group, the analgesic pump will be connected immediately after surgery. A solution of esketamine 1.5 mg/kg + sufentanil 2 µg/kg, diluted to 150 mL, will be administered continuously for 72 h at the background infusion and impact doses of 1 mL/h and 2 mL/time, respectively; the locking time will be 10 min. The control group will receive sufentanil 2 µg/kg that will be administered as per the esketamine group. The primary outcome will be the Hamilton Depression Scale (HAMD-17) score on the third day post-surgery (POD3). Secondary study indicators will include (1) visual analog scale (VAS) score and HAMD-17 score prior to surgery, immediately after entering the postanesthesia care unit (PACU) and 1, 2, 3, 4, and 5 days after surgery; (2) Richmond Agitation-Sedation Scale (RASS) score at 1, 2, 3, 4, and 5 days after surgery; (3) consumed doses of sufentanil and esketamine after surgery; (4) postoperative analgesia pump effective press times, rescue analgesia times, and rescue drug dosage, recording the number of rescue analgesia and rescue drug dosage at 6, 24, 48, and 72 h after the patient enters the PACU; (5) postoperative complications and adverse events; (6) postoperative hospital stay; (7) concentrations of brain-derived neurotrophic factor (BDNP), 5-hydroxytryptamine (5-HT), tumor necrosis factor (TNF-α) and interleukin-6, at 1, 3, and, 5 days post-surgery; and (8) the patient survival rate at 6 and 12 months post-surgery.

**Discussion:**

The study hypothesis is that the postoperative HAMD-17 and VAS scores, incidence of postoperative adverse reactions, and concentration of serum markers BDNP, 5-HT, TNF-α, and IL-6 in the experimental group will be lower than those in the control group.

**Trial registration:**

ClinicalTrials.gov ChiCTR2200066303. Registered on November 30, 2022.

Protocol version: 1.0

**Supplementary Information:**

The online version contains supplementary material available at 10.1186/s13063-023-07575-8.

## Background

Pancreatoduodenectomy (PD) is the standard surgical procedure for the treatment of precancerous lesions and some benign conditions in the pancreatic head, distal bile duct, ampulla, and duodenum. It is traumatic, difficult to perform, and has a high incidence of postoperative complications and perioperative mortality. Postoperative complications and pain occur frequently and affect the psychological status of patients. Patients who have undergone PD often experience symptoms of anxiety and depression. Studies have shown that the incidence rates of anxiety and depression in such patients are approximately 33.6 and 27.6%, respectively [1, 2]. Additionally, patients have high postoperative pain scores over a long duration, and their pain is difficult to treat [3]. The untimely treatment of postoperative depression and incomplete analgesia can prolong the hospital stay of patients and increase the incidence of complications and treatment costs, and postoperative pain may aggravate their symptoms of postoperative depression [1]. Therefore, more drugs and accurate models are needed to meet the urgent clinical demands of patients with intractable visceral pain.

The antidepressant effect of esketamine is related to its noncompetitive antagonism of the N-methyl-D-aspartate (NMDA) receptor. The cluster discharge signal of the “anti-reward center” of the lateral habenular nucleus of the brain enhances the inhibition of the “reward center” of the monoamine nuclei in the midbrain downstream of the lateral habenular nucleus, leading to depression [4]. Blocking the cluster discharge of neurons in the lateral habenular nucleus can relieve the excessive inhibition of the “reward center,” playing an antidepressant role [5]. Clinical trials have shown that esketamine can improve short-term depression and pain in patients with cervical cancer after surgery [6, 7]. Furthermore, pain and depression are strongly correlated. Acute and chronic pain are known risk factors for postoperative depression, and perfect postoperative analgesia is a key strategy to reduce the incidence of postoperative depression [8, 9]. Esketamine is DEX-ketamine-isolated and purified from ketamine; it is more powerful and has twice the anesthetic and analgesic effects than racemic ketamine. Ketamine can effectively relieve depression and anxiety [10–12]; thus, the study hypothesizes that the postoperative application of esketamine can effectively improve postoperative depression in patients undergoing PD.

Studies have shown that esketamine has multiple effects, such as antipleasure deficiency, reducing suicidal ideation, relieving anxiety, relieving bronchospasm, improving stress, treating chronic pain, protecting neurons, and improving neural plasticity and neuronal activity [13, 14]. Therefore, in patients undergoing PD, Esketamine could have an antidepressant effect, improve mood as a result of its superior analgesic effect, reduce the incidence of adverse reactions, and increase patient satisfaction. Hence, the aim of this study is to investigate the effect of esketamine on postoperative depression and pain in patients undergoing PD.

## Methods

### Study setting and design

This is an ongoing prospective, double-blind, parallel-group, allocation ratio 1:1, randomized controlled, non-inferiority trial conducted at the Department of Anesthesiology, Tianjin Medical University Cancer Institute and Hospital, Tianjin, China. The trial has been approved by the hospital’s Clinical Research Ethics Committee (E20221148). Written informed consent will be obtained from all patients included in the study. The Trial Steering Group and the independent Data Monitoring and Ethics Committee meet to review conduct throughout the trial period. This study was registered on the Chinese Clinical Trial Register Network (http://www.chictr.org/; registration number, ChiCTR2200066303, 30/11/22). The primary aim of the study is to investigate the effect of postoperative administration of esketamine on postoperative depression in patients undergoing PD. Secondary aims are to investigate the effect of esketamine combined with sufentanil on postoperative analgesia and evaluate the effect of esketamine on the incidence of postoperative adverse events and on the serum markers, brain-derived neurotrophic factor (BDNP), 5-hydroxytryptamine (5-HT), tumor necrosis factor alpha (TNF-α), and interleukin-6 (IL-6). The CONSORT flow diagram is shown in Fig. 1.

**Fig. 1 Fig1:**
[figure not shown]
Trial profile. *PCIA*, patient-controlled intravenous analgesia; *HAMD-17*, Hamilton Depression Scale; *VAS*, visual analog scale; *PACU*, postanesthesia care unit; *RASS*, Richmond Agitation-Sedation Scale; *BDNP*, brain-derived neurotrophic factor; *5-HT*, 5-hydroxytryptamine; *TNF-α*, tumor necrosis factor; *IL-6*, interleukin-6

### Inclusion criteria

(1) Age: 18–65 years, regardless of sex; (2) American Society of Anesthesiologists (ASA) Class I–III; (3) elective PD to be scheduled; (4) No other surgical contraindications; and (5) can clearly understand and voluntarily participate in the study and sign the informed consent form. If patients are willing to participate, they will be evaluated by Mini-Mental State Examination (MMSE), Hamilton Depression Scale (HAMD-17) [15], and Richmond Agitation Sedation Scale (RASS) [16] before surgery after they sign the informed consent form.

### Exclusion criteria

(1) Opioid analgesics were administered before surgery; (2) drug use or alcohol or drug abuse; (3) patients with preoperative cognitive impairment based on a Mini-Mental Scale Exam scale (normal cut-off value: > 23 points); (4) history of severe cerebrovascular disease; (5) mental illness, patients with a clear diagnosis of depression and long-term drug treatment; (6) no written informed consent for the study and/or no acceptance to have PD surgery; (7) sensitivity to esketamine and related drugs; (8) previous contraindications to ketamine use (e.g., severe refractory hypertension, cor pulmonale, hyperthyroidism, epilepsy, increased intraocular pressure, increased intracranial pressure, intracranial space-occupying lesions, and a history of cerebrovascular accidents); and (9) the investigator thinks that the patient should not participate in this trial.

### Randomization and blinding

All researchers, patients, and analysts will be blinded. Randomization is conducted using a computer-generated blocked randomization sequence. SPSS 21.0 (IBM SPSS, Armonk, NY, USA) will be used to generate a random code table according to the total number of subjects, number of groups, proportion between groups, and length of the block. All participants that meet the inclusion criteria are randomly assigned to either the experimental or control group at a ratio of 1:1, using numbered, sealed, and opaque envelopes. Participants will be grouped and assigned in numerical order. Patient, anesthesia, and postoperative recovery data are written in the case report forms (CRFs). The blind will not be broken during the trial, unless there is significant reason to do so. The outcome will be assented by assessors, and the data will be analyzed by independent statisticians; the outcome evaluation and statistical analysis will be announced independently and blinded. All original records including informed consent and CRFs together with related letters will be retained for 10 years and then destroyed according to the requirements of the hospital.

### Dropout criteria

(1) Patients who voluntarily withdraw their informed consent at any time during the study; (2) failure to complete treatment as planned or refusal of postoperative neuropsychological evaluation; (3) any clinical adverse event or other medical condition in which the continued use of the drug may no longer benefit the subject; (4) lack of main indicators and obvious incomplete data; (5) the efficacy will not be evaluated for cases removed from the group because of adverse reactions, but the adverse effects of treatment should be included in the statistics; and (6) other reasons that the investigators believe may justify the discontinuation of the trial.

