### Data collection and follow-up period

The primary outcome measure would be the HAMD-17 score on the third postoperative day. Secondary study indicators include (1) the visual analog scale (VAS) and HAMD-17 scores prior to surgery, immediately after entering the PACU, and 1, 2, 3, 4 and 5 days after operation; (2) RASS score when the patient enters the operating room and at 1, 2, 3, 4 and 5 days after surgery; (3) the dosage of sufentanil and esketamine after surgery; (4) postoperative analgesia pump press times, rescue analgesia times, rescue drug dosage, and number of rescue analgesia times and rescue drug dosages at 6, 24, 48, and 72 h after the patient entered the PACU; (5) postoperative complications and adverse events; (6) postoperative hospital stay; (7) concentrations of brain-derived neurotrophic factor (BDNP), 5-hydroxytryptamine (5-HT), tumor necrosis factor (TNF-α), and interleukin-6 at 1, 3, and 5 days post-surgery; and (8) the patient survival rate at 6 and 12 months post-surgery. The intervention is self-regulated, and the authors are monitoring usage. Nurses in the ward will be responsible for assisting in the follow-up study of medication to ensure patient compliance. Implementing the esketamine or control group will not require alteration to usual care pathways (including the use of any medication), and these will continue for both trial arms.

Safety end-point measures will include incidence, severity, and causality of reported serious adverse events (SAEs), namely changes in the occurrence of the expected common prematurity complications and clinical laboratory test assessments, and the development of unexpected SAEs in this high-risk population. All SAEs will be followed until a satisfactory resolution or until the investigator responsible for the care of the participant deems the event to be chronic or the patient to be stable. All expected and unexpected SAEs, whether or not they are attributable to the study intervention, will be reviewed by the principal investigator and all authors to determine if there is a reasonable suspected causal relationship to the intervention. If the relationship is reasonable, SAEs will be reported to the Ethics Committee to guarantee the safety of participants.

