### Sample size calculation

The clinically meaningful beneficial effect of esketamine on the depressive symptoms of patients undergoing surgery is unclear. The minimum clinically important difference was at least 20%; however, differences in response rates range from approximately 26 to 56% among patients with major depressive disorder [17]. Therefore, we assumed that for surgical patients, the third postoperative day response rate difference would be 30% between the two groups. Likewise, for the control group, a response rate of 10% was assumed. A total of 38 patients in each group would provide 80% power with a two-sided type-I error of 0.05. The test-group-to-control-group ratio is 1. Considering an overall withdrawal rate of 5%, a sample size of 80 patients is considered adequate [10]. If data are missing, we will use multiple imputation methods to fill in according to the research needs.

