### Statistical methods

Statistical analysis will be carried out using the “intention to treat” method; all data will be collected in a single database and analyzed to evaluate any differences between the randomized groups for both primary and secondary outcomes. SAS 9.4 (SAS Institute, Cary, NC, USA) statistical software will be used for all statistical analysis. All statistical tests are two-tailed. *P*-values ≤ 0.05 will be considered statistically significant. Normally distributed data will be described as mean ± standard deviation, and the analysis of variance will be used for comparison between groups. Non-normally distributed data will be described as median (minimum–maximum), and the rank-sum test will be used for comparison between groups. The counting data are statistically described by frequency (composition ratio), and the *χ*^2^ test or exact probability method will be used for comparison between groups. The rank-sum test will be used for the inter-group comparison of grade data.

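### Excluding patients removed for adverse reactions from efficacy evaluation contradicts intention to treat; item (4), and possibly item (2), also conflict with imputation

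*Protocol article*

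**What the plan says.** Three sections of the protocol article bear on who enters the efficacy analysis.

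- **Dropout criteria.** Item (5) states that "the efficacy will not be evaluated for cases removed from the group because of adverse reactions"; the adverse effects of those patients are still counted. Item (2) lists "failure to complete treatment as planned or refusal of postoperative neuropsychological evaluation". Item (4) lists "lack of main indicators and obvious incomplete data".
- **Statistical methods.** "Statistical analysis will be carried out using the “intention to treat” method", applied to differences between the randomised groups for primary and secondary outcomes.
- **Sample size calculation.** "If data are missing, we will use multiple imputation methods to fill in according to the research needs". The same paragraph allows for 5% withdrawal.

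On timing, Data collection and follow-up period says: "The primary outcome measure would be the HAMD-17 score on the third postoperative day". According to the abstract, the study solution "will be administered continuously for 72 h". No section reconciles these statements or assigns the exclusions to a separate per-protocol set.

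**The concern.** Item (5) is a rule about the analysis, not only about treatment: the patient counts for safety but not for efficacy. Intention to treat requires the opposite. Item (4) makes an absent primary outcome a ground for dropout, which is the situation imputation exists to handle.

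The arms differ only by esketamine, so removal for adverse reactions can depend on the assigned treatment even when all staff are blinded. The pump runs for 72 h and the primary outcome is read on day 3, so removals during the infusion fall at or before the primary assessment. The patients left for comparison may then no longer be the groups that randomisation made alike. Two analysts could also follow different sentences of the same protocol and report different primary results.

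**Working it through.** **1. The texts side by side**

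| Situation | Dropout criteria | Other sections | Compatible? |
|---|---|---|---|
| Removed for an adverse reaction | Efficacy not evaluated (item 5) | Analysed as randomised (Statistical methods) | No |
| Main indicator missing | Dropout (item 4) | Imputed (Sample size calculation) | Only if dropout does not mean leaving the analysis, and item (4) has little other meaning |
| Treatment incomplete or assessment refused | Dropout (item 2) | Analysed as randomised; missing score imputed | Yes, unless dropout means leaving the analysis |

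**2. The plan's own sample size.** Inputs from Sample size calculation: control response 10% and "the third postoperative day response rate difference would be 30% between the two groups", hence 40% vs 10%; 80% power; two-sided 0.05; ratio 1.

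n = [1.960·√(2·0.25·0.75) + 0.842·√(0.10·0.90 + 0.40·0.60)]² / 0.30² = 31.5, or 32 per group.

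With continuity correction: (31.5/4)·[1 + √(1 + 4/(31.5·0.30))]² = 37.9, or 38 per group. Then 38/0.95 = 40 per group, 80 in total. The stated figures reproduce. The withdrawal allowance is 80 − 76 = 4 patients.

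**3. Bias on the HAMD-17 scale.** The documents give no removal rates and no scores for removed patients, so f and c below are assumptions. Suppose there is no true difference, 40 patients per arm, a fraction f of one arm is removed, and their scores are c SD worse.

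- Worse than the full-arm mean: the retained mean shifts by f·c/(1 − f) SD.
- Worse than the retained patients: it shifts by f·c SD.

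Type I error is the two-sided t-test rejection rate with 40(1 − f) against 40 patients. The noncentrality is shift × √[n₁n₂/(n₁ + n₂)]. Removal is from the esketamine arm only.

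| f | c | Shift, full-arm reference | Type I error | Shift, retained reference | Type I error |
|---|---|---|---|---|---|
| 0.10 | 0.5 | 0.05/0.90 = 0.056 | about 5.5% | 0.05 | about 5.4% |
| 0.15 | 1.0 | 0.15/0.85 = 0.176 | about 12% | 0.15 | about 10% |
| 0.20 | 1.0 | 0.20/0.80 = 0.25 | about 18% | 0.20 | about 13% |

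With equal f and c in both arms the shifts cancel and the bias is 0. If the removals are in the control arm instead, the same shifts run against esketamine.

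**4. Bias on the response scale, with removals in both arms.** Assume no true difference and that removed patients are non-responders. The bias is p/(1 − f_E) − p/(1 − f_C), where E is esketamine and C is control.

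- 10% vs 2.5% removed: 0.9 points at p = 10% (0.1111 − 0.1026) and 3.4 points at p = 40% (0.4444 − 0.4103).
- 20% vs 5% removed: 2.0 points (0.1250 − 0.1053) and 7.9 points (0.5000 − 0.4211).

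If removed patients respond like the others, the bias is 0. If they respond 1.5 times as often, the last case becomes −3.9 points (0.3500 − 0.3895).

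**5. Under the design effect.** Let evaluated patients respond at 40% vs 10% and removed patients not at all. With 20% vs 5% removed, the difference among all randomised patients is 0.40·0.80 − 0.10·0.95 = 22.5 points, with about 71% power at 40 per group (uncorrected formula). The analysis with exclusions still shows 30 points.

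**The case against.** Several objections are fair.

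- **Only item (5) mentions efficacy evaluation.** A reader might infer that every dropout criterion removes the patient from the analysis. The text does not say so. Dropout and imputation can coexist: a patient refuses assessment, the score is missing, and it is imputed. This stands for item (2). It is weaker for item (4), which is hard to read except as removal from the analysis.
- **The direction is not given.** A reader might infer a bias toward esketamine. That needs more removals in that arm and worse scores among those removed, and the documents supply neither. The abstract's hypothesis and the Discussion expect fewer adverse reactions with esketamine, and both arms receive sufentanil. This stands.
- **The one-arm figures are an extreme case.** No document supports zero removals in the control arm, and the mild corner of the table is close to the nominal 5%. This stands, so the figures only illustrate what could happen.
- **Sample loss.** A reader might infer that the exclusions will exceed the 5% allowance. No rate is stated. Removing 10% of one arm is 4 patients, which equals the allowance.
- **A fuller protocol or analysis plan may settle it.** It might choose one rule, but the published text would still state rules that conflict. This objection does not remove the point.

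**Conclusion.** The point holds in a limited form. The firm contradiction is item (5) against the intention-to-treat commitment. Item (4), and by implication item (2), conflict with multiple imputation only if dropout is read as removal from the analysis.

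Following item (5) as written allows a post-randomisation exclusion that can bias the primary comparison either way. Its size is unknown. The illustrative range is 0.06–0.25 SD and a type I error of about 5.5–18%, or 0.05–0.20 SD and about 5.4–13% if removed patients are compared with retained ones. Both ranges rest on assumed removals of 10–20% in the esketamine arm alone. The documents do not support a definite bias toward esketamine or a definite loss beyond the 5% allowance. The contradiction needs correcting whichever way the bias would run.

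**What to change.** Reconcile the Dropout criteria with Sample size calculation and Statistical methods before unblinding:

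1. Delete the efficacy exclusion in item (5), and delete item (4) as a ground for leaving the analysis. State that meeting item (2) does not remove a patient from it either.
2. Keep collecting HAMD-17 after study drug is stopped, unless consent is withdrawn.
3. Analyse all randomised patients in their assigned arm. Make multiple imputation of missing day-3 scores the fixed rule, not one that depends on need.
4. Label any analysis with exclusions as a sensitivity analysis.

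The clinical rules on when study drug is stopped stay as they are and are not judged here. The list should not be recast wholesale as stopping rules, which would make no sense for withdrawn consent or a refused assessment. N stays 80. The cost is a wording amendment plus minor in-hospital follow-up.

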### Treatment implementation

To the best of our knowledge, there are no reports in the literature on the dosage of esketamine for postoperative analgesia in patients undergoing PD. Thus, we carried out a preliminary experiment in four groups with five people in each (E20210966A). The doses of the three test groups were 1.0 mg/kg of esketamine + 2 μg/kg of sufentanil; 1.5 mg/kg of esketamine + 2 μg/kg of sufentanil; and 2.0 mg/kg of esketamine + 2 μg/kg of sufentanil, respectively. The control group received 2 μg/kg of sufentanil. These drugs were diluted to 150 mL using 0.9% saline. Patient-controlled intravenous analgesia was used with the background infusion and impact doses of 1 mL/h and 2 mL/time, respectively, administered continuously over 72 h. The locking time was 10 min. The frequencies of postoperative analgesia pump pressing and rescue analgesia were outcome indicators. There were no statistically significant differences in the frequency of analgesic pump presses and number of remedial analgesia between groups; the preliminary experimental results showed that the test group had the best analgesic effect with esketamine 1.5 mg/kg and sufentanil 2 μg/kg (Table 1).

**Table 1 Tab1:** Experimental results

**Number**	**Gender**	**Age (year)**	**Height (cm)**	**Weight (kg)**	**Other underlying diseases complicated before surgery**	**Preoperative MMSE score**	**Remedy analgesic frequency and medication**	**Number of effective compressions of analgesic pump**	**Total number of remedial analgesia + number of effective compressions of analgesia pump**
